## Abstract

**Background:**

One of the most prevalent long-term consequences of surviving breast cancer is fear of cancer recurrence (FCR), which is associated with higher (mental) healthcare costs and lower surveillance rates. The majority of breast cancer survivors report a need for professional help in dealing with FCR. An easy-accessible and cost-effective evidence‐based psychological intervention for reducing FCR is lacking. In the current study an online self-help training to reduce FCR will be evaluated. In addition, the secondary aim of this study is to identify factors that predict whether women can benefit from the online self-help training or not.

**Methods/Design:**

A multi-centre, parallel-groups, randomised controlled trial will be conducted to evaluate the (cost-) effectiveness of the CAREST-trial. A sample of 454 women with curatively treated breast cancer will be recruited from 8 hospitals in the Netherlands. Participants will be randomised to the intervention or usual care group (1:1). Self-report measures will be completed at baseline, 3 (post-intervention), 9, and 24 months. Primary outcome is FCR severity; secondary outcomes are healthcare costs, health status, and psychological distress. The online tailored self-help training “Less fear after cancer” is based on cognitive behavioural therapy and consists of 2 basic modules (psycho-education; basic principles of cognitive behavioural therapy) and 4 optional modules (rumination; action; relaxation; reassurance) to choose from. Each module consists of an informative part (texts, videos, audio files) and a practical part (exercises). For every patient, the intervention will be available for three months. Personal online support by an e-mail coach is available.

**Discussion:**

Online self-help training may be an easy-accessible and cost-effective treatment to reduce the impact of FCR at an early stage in a large group of breast cancer survivors. A strength is the 24 months follow-up period in the health economic evaluation. The results of the study will provide information on the possible strengths and benefits of online self-help training for FCR in breast cancer survivors.

**Trial registration:**

This study is registered at the Netherlands Trial Register (NTR4119, date registered: August 15, 2013).

## Background

Due to earlier diagnosis and improved medical treatments, the number of women living with breast cancer is rising. In the Netherlands, the prevalence of breast cancer has been estimated to rise from 100.000 in 2000 to 140.000 in 2020 [1]. Similarly, in the USA, the 5-year relative survival rate of women with breast cancer improved from 75 % in 1975 to 90 % in 2009 [2]. One of the most prevalent long-term consequences of surviving cancer is fear of cancer recurrence (FCR), which can be defined as the fear or worry of the possibility that the cancer will return or progress in the same organ or in another part of the body [3]. Although the majority (82 %) of long-term breast cancer survivors reported low levels of FCR, a considerable amount of women (17 %) reported moderate to high FCR [4]. In younger (age 18–45) early-stage breast cancer survivors, 70 % of participants report moderate to high levels of FCR [5]. Younger age was also found to be associated with a higher intensity of FCR [5, 6]. Moderate to high levels of FCR have also been found in 29 % of women with ductal carcinoma in situ or early invasive breast cancer two years after diagnosis [7].

Findings on the long-term course of FCR are still unclear [8]. Thewes and colleagues [9] found longer time associated with reduced FCR in younger cancer patients. Several other studies found no significant relationship between time since diagnosis and FCR [3, 10–15]. Elevated levels of FCR represent a continuing problem in cancer patients, up to sixteen years after diagnosis [3, 10–15]. For example, long-term breast cancer survivors (5–12 years after diagnosis) report many factors that can trigger FCR, such as hearing about cancer, unclear bodily complaints, environmental triggers (e.g., on television, the internet, newspapers, and magazines; and visiting a doctor [16]. Women encounter these triggers about twice a month [16].

Thus, FCR is a common and continuing problem in breast cancer survivors. Women cope with FCR in different ways. Elevated levels of FCR has been found to be associated with higher frequency of unscheduled visits to the general practitioner, larger number of outpatient and emergency room visits, and more use of health care services [5, 16, 17]. Higher levels of FCR may also lead to avoiding forms of cancer screening and medical control visits [5, 16, 17]. Moreover, FCR may lead to various types of (compulsive) self-examining [5, 16, 17]. Therefore, it is not surprising that preliminary evidence shows that FCR is associated with higher healthcare costs and lower surveillance rates, which may compromise health outcomes [5].

Depending on the coping mechanisms used by breast cancer survivors to deal with their FCR, FCR also has a considerable impact on their lives. One of the most significant effects of FCR is the negative impact on quality of life [4, 18, 19]. Furthermore, FCR may have a correlation with distress, intrusive thoughts, avoidance, hyperarousal, psychological disorders (e.g., depression, anxiety symptoms, posttraumatic stress disorder), and fatigue [3, 4, 13, 14, 20]. Subsequently, FCR is associated with higher mental health costs [5, 19].

Cancer survivors frequently identify FCR as a major concern and 20 to 79 % of them report to have a need for professional help coping with FCR [19, 21]. About 30 % of cancer survivors have indicated that there is no support for them in dealing with FCR [22]. Reasons for this include lack of recognition, lack of trained mental health professionals, insurance coverage and cost issues, and geographical distance from providers [22, 23]. Considering the increasing prevalence of breast cancer, increasing healthcare costs, and the lack of professional help for FCR in a large group of cancer survivors [1, 2, 5], there is an urgent need for easy-accessible and cost-effective evidence‐based psychological interventions for reducing FCR.

Knowledge on treatment of FCR is limited. Simard and colleagues [19] found only five face-to-face group interventions (cognitive behaviour therapy, supportive-experiential therapy, mindfulness-based stress reduction, and emotion regulation) to reduce FCR. Furthermore, Völker and colleagues [24] suggest a stepped-care model for treating FCR. Normalization, psycho-education and self-management are the first steps in this model [24]. Normalization helps patients to understand that fear is a normal reaction which can be helpful in some situations. Psycho-education is necessary, because cancer survivors experience many bodily symptoms (such as fatigue, new aches and pains, muscle tension, joint stiffness, feeling of weakness, indigestion, and other physical symptoms) that can easily be misinterpreted as symptoms of recurrence [16]. Anxiety itself also can cause several bodily symptoms (such as increased heart rate, shortness of breath, chest pressure, sweating, dry mouth, dizziness, feeling of weakness, muscle tension, and indigestion), which may increase other bodily symptoms and therefore reinforce FCR. In extreme cases, FCR has been associated with the development of anxiety disorders [8]. Misinterpretation of bodily symptoms can lead to negative thinking, which causes somatic amplification. Because of this somatic amplification, patients focus even more on their bodily symptoms, leading to a negative emotional spiral. With psycho-education, patients gain more knowledge about the bodily mechanisms of fear. This knowledge can help them to break the negative spiral. Ziner and colleagues [25] found that breast cancer survivors with high self-efficacy in dealing with concerns related to breast cancer after treatment, had lower FCR and that self-efficacy may have a protective effect in these women. Therefore, training in self-efficacy may reduce FCR [24–26]. If these first steps of treatment for FCR turn out to be insufficient, cognitive behavioural therapy (CBT) should be the next step in the treatment of FCR [24, 27, 28]. Furthermore, acceptance focused therapies, such as Mindfulness Based Stress Reduction (MBSR), Mindfulness Based Cognitive Therapy (MBCT) and Acceptance and Commitment Therapy (ACT) may be included in treatment for FCR [24].

In order to reach the growing group of breast cancer survivors experiencing FCR, a CBT-based online self-help intervention (including normalization, psycho-education and self-management) may be an appropriate and accessible way to offer psychological treatment to patients for several reasons. First, self-help without support was the second most preferred type of supportive care by cancer patients (14–28 %), after individual professional counseling [21]. Furthermore, there is a growing body of evidence that internet interventions can improve psychological well-being in cancer patients [23]. Online self-help interventions have several advantages, including convenience (such as working on the self-help training in the evening when there are no competing demands), ability to proceed at one’s own pace to master the material, low cost, greater privacy and confidentiality, more comfort, the intervention content can be updated quickly, greater accessibility (for example for those living in rural areas), time- and cost-effective, and where waiting lists are long [23, 29–31]. Convenience and working in their own pace may be particularly attractive for young women, who often are still working and have young children [5]. Given the high prevalence of FCR in young breast cancer survivors, online self-help training may be an effective and attractive way to reach these young women [5]. Moreover, an informational self-management intervention may reduce psychological distress (feelings of tension, anger and depression) in high risk patients who perceive little control and much illness uncertainty [32]. Thus, an online self-help intervention with psycho-education may empower patients. Disadvantages of online self-help interventions are internet access constraints, technical difficulties, high drop-out rates, poor adherence, safety issues, limited personal interaction, and not being able to detect more complicated issues and non-verbal or verbal clues in patients [23, 31, 33, 34]. Furthermore, online cognitive behavioural interventions for anxiety have been found to be effective for anxiety disorders and anxiety symptoms [30, 35]. Online cognitive behavioural self-help interventions for anxiety have been found to be at least as good as face-to-face treatment in several studies, but other studies found small effects favoring face-to-face treatment [29, 34–37]. Self-help interventions may be specifically effective, if based on a theoretical model such as CBT [38]. In conclusion, CBT-based online self-help interventions are promising and may provide effective, acceptable, and practical health care for those who may otherwise remain untreated. Because online self-help training may be both easily accessible and cost-effective, in the current study an online CBT-based self-help training to reduce FCR after breast cancer treatment will be evaluated.

### Aims

The primary aim of the CAncer REcurrence Self-help Training [CAREST] randomised controlled trial is to evaluate the effectiveness and cost-effectiveness of the online CBT-based self-help training “Less fear after cancer” [in Dutch: “Minder angst bij kanker”] in reducing FCR in women with curatively treated breast cancer (breast cancer survivors), compared to usual care. Specific hypotheses are that:FCR severity reduces more in the online self-help condition compared to the usual care condition between baseline and follow-up (3 months). This effect will sustain 9 and 24 months after baseline. Small effect sizes are expected.Health care costs reduce more in the online self-help condition compared to the usual care condition between baseline and 24 months after baseline.Psychological distress reduces more in the online self-help condition compared to the usual care condition between baseline and 3 months after baseline. These effects will sustain 9 and 24 months after baseline.

Online self-help for FCR is not expected to be effective for all participants. Several factors, such as level of FCR, psychological distress, coping strategies, and perceived self-efficacy may predict if women can benefit from the online self-help training. Therefore, the secondary aim is to identify factors that predict whether women can benefit from the online self-help training or not.4.With regard to prediction of treatment effect we will explore the following hypotheses:*Baseline fear of recurrence severity*. In participants with low scores on FCR severity there is no need for psychological help, these participants are expected not to use the online self-help training or to drop-out. In participants with moderate scores on FCR severity a modest effect of the online self-help training is expected. In participants with high scores on FCR severity there will be a modest effect of the self-help training and additional need for psychological help or guidance by a therapist.*Psychological distress*. In participants with high scores on psychological distress extra psychological help will be needed, because psychological distress may interfere with self-management capacity. Participants with moderate scores on psychological distress will have enough motivation for self-help training. Participants with low scores on psychological distress are expected to have minimal motivation for self-help training and thus a low treatment effect.*Level of functioning impairment*. In participants with high scores on level of functioning impairment extra psychological help will be needed. Participants with moderate scores on level of functioning impairment will have motivation for self-help training. Participants with low scores on level of functioning impairment will have minimal motivation for self-help training.*Coping strategies*. The relation between coping and treatment effect will be explored.*Psychosocial problems and risk factors*. If participants score high in many problem domains extra help may be needed. Moreover, high scores on trait anxiety and low scores on social support indicate that extra psychosocial help may be needed.*Perceived self-efficacy for online self-help.* Participants with low scores on perceived self-efficacy for online self-help may have poor self-management skills. Treatment effect for these participants will be minimal and extra support may be needed. For participants with moderate and high scores on perceived self-efficacy for online self-help, the training which is being investigated will be appropriate and will lead to moderate treatment effect.*Socio-demographic variables* with respect to treatment effect will be explored. For example, for young women and women with a partner, online self-help training may be more effective than older participants or those without a partner. Also, for medium to highly educated women the self-help training may be more effective.*Medical variables* with respect to treatment effect will be explored.

## Methods/Design

The CAREST-study design and intervention will be reported in accordance with the CONSORT statements for eHealth interventions [39] and parallel group randomised trials [40], the SPIRIT 2013 statement [41, 42], and in accordance with the recommendations and guidelines for internet intervention research in psycho-oncology [23].

### Study design

The CAREST-study is a multi-centre, randomised controlled trial, comparing online self-help training with care as usual in breast cancer survivors. A sample of 454 women with curatively treated breast cancer will be recruited from 8 hospitals scattered over the Netherlands. The participating hospitals are the Maasstad hospital in Rotterdam, St Antonius hospital in Utrecht, Admiraal de Ruyter hospital in Vlissingen, Reinier de Graaf hospital in Delft, Antonius hospital in Sneek, St. Elisabeth hospital in Tilburg, Catharina hospital in Eindhoven, and UMCG in Groningen (all situated in the Netherlands). After completion of the baseline measure, women will be randomised to either the online self-help or control group. Follow-up assessments are at 3 months (post-intervention), 9 months, and 24 months after baseline. Additionally, every 3 months participants will be asked to fill out a short measure about their healthcare use. Two reminders will be sent by e-mail one and two weeks after the first invitational e-mails. Eventually, participants who do not complete the questionnaires will receive a phone call from the researcher to remind them.

### Participant eligibility

Women are eligible to participate if they had a diagnosis of breast cancer 1–5 years ago; have no signs of local or regional recurrence or metastatic disease; are capable of filling out questionnaires in Dutch; if their age at disease onset was 18 years or older; and if they have access to a computer with an internet connection. There are no exclusion criteria.

### Recruitment settings and procedure

Patients will be recruited in two ways. First, four hospital sites are expected to recruit participants through oncology nurses, nurse practitioners, or oncologists, who will ask eligible patients to participate in the study. These patients will be informed about the study during their regular check-up at the outpatient clinic. When women show interest in participating in the study, they receive a comprehensive information letter. In three hospitals patients will be phoned by the researcher two weeks after receiving the information letter. They will be asked whether they have any questions and if they are interested to participate in the study. Second, the remaining four hospital sites are expected to recruit participants by a comprehensive information letter sent to them by mail. These patients will also be phoned by the researcher about two weeks after receiving the information letter to ask whether they are interested to participate in the study. When patients decide to participate, they are asked to return the included informed consent form with the reply-paid envelope within a week. Moreover, all participants will be informed about the possibility for psychological counseling nearby, so they know where to turn to in case they need (more) help.

### Randomisation

After completing the baseline measure, every patient will be randomly assigned to either the online self-help training or care as usual with an allocation ratio of 1:1. Block randomisation (block size 10) will be carried out through a sealed envelope system, for each hospital separately. Both the participants and the researchers are blinded for the randomisation process, but not for the randomisation outcome. Statistical analysis will be done by a statistician blind for randomisation outcome.

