**Fig. 1 Fig1:**
[figure not shown]
Screenshot of the “Less fear after cancer” online self-help training

The most important functionality of the online self-help training “Less fear after cancer” is the worksheet, because it gives an overview of the modules and access to the intervention. By clicking on a module, participants can access the information (texts, videos, audio files) and exercises of the self-help training. Other functionalities include a library with the information and forms in pdf format, videos, audio files, and a mailbox for technical assistance.

“Less fear after cancer” is fully automated and primarily non-guided and is delivered without professional support from a therapist. In this study, personal online support by an e-mail coach (the researcher) is available for the women that indicate a need for this. The e-mail coach can give technical assistance and eventually refer participants to their general practitioner or medical specialist when they indicate a need for professional help.

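### Fixed blocks of 10 per hospital, with allocations visible to the researchers, let at most about one allocation in six be deduced just before the draw, and fewer at the recruitment call

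*Protocol article*

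**What the plan says.** The Randomisation section of the protocol article fixes the scheme. Each woman, after completing the baseline measure, is "randomly assigned to either the online self-help training or care as usual with an allocation ratio of 1:1". The method is: "Block randomisation (block size 10) will be carried out through a sealed envelope system, for each hospital separately". On blinding it says: "Both the participants and the researchers are blinded for the randomisation process, but not for the randomisation outcome".

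Two other sections bear on this:

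- **Recruitment settings and procedure.** Of the four hospitals that recruit in clinic: "In three hospitals patients will be phoned by the researcher two weeks after receiving the information letter". Of the four that recruit by mail: "These patients will also be phoned by the researcher about two weeks after receiving the information letter". In both cases the call asks whether the woman wants to take part. Researcher calls are therefore stated for seven of the eight hospitals.
- **Intervention.** In the training arm "personal online support by an e-mail coach (the researcher) is available for the women that indicate a need for this".

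The article describes only one block size.

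**The concern.** A sealed envelope hides its own contents. It does not hide what can be inferred from the envelopes already opened. With one fixed block size, a separate sequence per hospital and known past allocations, the end of each block can be worked out by counting. The statement that researchers are blinded to the process therefore protects less than it suggests, because they see the outcomes and the block size is printed in the article.

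Allocation is open and the primary outcome, the FCRI severity subscale, is self-reported. If someone who speaks to candidates can foresee the next arm, the two groups could come to differ in motivation or in other traits that the baseline FCRI score does not capture.

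**Working it through.** The article gives no figure for predictability, so there is none to reproduce.

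**Inputs.** Block size 10, 1:1, hence m = 5 per arm in each block; separate sequence per hospital (Randomisation). 454 women in 8 hospitals (Study design). An even spread, 454/8 ≈ 57 per hospital, is my assumption.

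**1. Certain allocations in a complete block.** Allocation k is certain if one arm already has five among the first k − 1:

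P(k) = 2·C(k−1, 5)/C(10, 5), with C(10, 5) = 252.

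| Position | P(certain) |
|---|---|
| 6th | 2·1/252 = 0.8% |
| 7th | 2·6/252 = 4.8% |
| 8th | 2·21/252 = 16.7% |
| 9th | 2·56/252 = 44.4% |
| 10th | 2·126/252 = 100% |

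The sum is 2·210/252 = 1.667 per block, so the share is 1.667/10 = 16.7%. This agrees with the general result 1/(m+1) = 1/6 and with enumeration of all 252 sequences.

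**2. Incomplete last block.** With 57 women there are five full blocks and seven women of a sixth: (5 × 1.667 + 0.008 + 0.048)/57 = 14.7%. With six hospitals of 57 and two of 56, about 67 of 454 (14.8%) are certain.

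**3. Best guess.** Always guessing the arm with fewer allocations so far is right with probability (5 + 2⁹/252 − 0.5)/10 = 65.3%, against 50% by chance.

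**4. At the recruitment call.** Steps 1–3 apply just before the envelope is opened. If L other women at the same hospital are randomised between the call and the draw, only the first k − 1 − L allocations are known at the call:

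- L = 1: 2·(1 + 6 + 21 + 56)/252 = 0.667 per block, or 6.7%
- L = 2: 2·(1 + 6 + 21)/252 = 0.222 per block, or 2.2%
- L = 3: 2·(1 + 6)/252 = 0.056 per block, or 0.6%

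The article does not give the delay. As an illustration, even accrual over two years gives 454/8/104 ≈ 0.55 women per hospital per week. A delay of two to three weeks (assumed) then means between one and two intervening women.

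**5. Varied block sizes.** With sizes 8, 10 and 12 chosen at random, the certain share depends on what the observer knows:

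- knows the set of sizes but not where later blocks start: about 1%
- knows where the current block began but not whether it has ended: 2.9%
- is told, as it happens, when each new block starts: about 5%

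The best-guess rate stays near 65%.

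**The case against.** The strongest reply is that the exposure is small and much of it theoretical.

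- **Timing.** The call comes first, then the consent form, then the baseline measure, and only then the draw. A caller who knows the current tally does not know how many women will be randomised before this one. This stands: one in six is not the share known at the call.
- **Room for selection.** There are no exclusion criteria, every woman who completes baseline is randomised, baseline is self-completed before allocation, and the primary comparison adjusts for baseline level. This stands too. What remains is uneven encouragement to consent or complete baseline, or the order of entry, acting on traits that baseline severity does not capture.
- **Block size.** Ten is already fairly large: the same formula gives 33% for blocks of 4 and 25% for blocks of 6. True, but one fixed size still makes the tenth allocation of every complete block certain.
- **Staff and list-holding.** A reader might infer that one person calls, coaches and tracks allocations, or that nobody independent holds the list. The documents support neither. The article uses both the singular and the plural for the researchers, and who generates the list and holds the envelopes is something a condensed article commonly omits. An independent holder would prevent tampering, but not deduction from known outcomes.
- **Size of the gain.** Varied blocks leave the best-guess rate almost unchanged. Correct: the gain is the removal of most certain allocations.

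**Conclusion.** The point holds in a limited form. Just before the draw, at most about one allocation in six (16.7% for complete blocks, about 15% with 57 women per hospital) can be deduced by someone who knows the block size and follows that hospital's tally. At the recruitment call the share is lower: 6.7% or 2.2% if one or two other women are randomised in between.

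A reader might infer that one woman in six was recruited with her arm already known, or that allocation was in fact influenced. The document supports neither. The figure describes what can be deduced at the draw, not what anyone did. It also does not say whether the callers knew the block size or kept a tally. No size of bias in the outcome can be derived.

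The result rests on 1:1 blocks of exactly 10. The 15% also assumes an even spread over hospitals, and the figures at the call depend on an unstated delay. This is a worthwhile, low-cost improvement and does not by itself threaten the primary comparison.

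**What to change.** For allocations still to be made, use randomly varied block sizes within each hospital (for example 8, 10 and 12), and do not disclose the sizes to those who recruit or coach.

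The cost is a new allocation list and new envelopes. Sample size is unaffected. Possible imbalance within a hospital rises slightly: a block of 12 allows a difference of 6 part-way through, against 5 for a block of 10, and the switch may leave one incomplete block in each of up to eight hospitals. Inclusion began in April 2014 and was expected to take up to two years, so the benefit depends on how many allocations remain. If none do, the trial report can state whether those who phoned candidates knew the block size.
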